#### *Confirmation of diagnosis*

All women will have a MINI International Neuropsychiatric Interview (MINI, Version 6.0.0) by a trained, blinded research team member skilled in diagnostic interviews within 1 week of completing their psychosocial assessment. The MINI is a brief, ‘gold standard’ diagnostic interview designed to assess the presence of mental disorders according to criteria defined in the Diagnostic and Statistical Manual of Mental Disorders IV (DSM-IV) [49]. It can be administered in approximately 15 minutes with interviewees providing yes/no responses. All research staff conducting diagnostic interviews will participate in four 3-hour training sessions on the structure and completion of the MINI, interviewing skills, approaches to asking sensitive questions, and role-playing. Additionally, the first two to three interviews will be supervised by one of the mental health clinicians on our team (KMH).

For women recruited through the maternity clinics, a research team member not involved in recruitment will conduct a telephone-based MINI within 1 week of the woman completing the psychosocial assessment (at the clinic). Because of space and time constraints in the maternity clinics, it is necessary to conduct the MINI via telephone, and follow-up by a different research assistant maintains blinding. For women recruited through the inpatient antenatal unit, the MINI will be conducted at the time of recruitment, after completion of the psychosocial assessment and baseline questionnaire. The research assistant involved in recruitment will conduct the MINI, with specific measures employed to maintain blinding (see Procedures).

#### *Outcomes and measurement*

##### 

**Primary outcome** The primary outcome is feasibility and acceptability of screening (for example, e-screening *versus* paper-based screening) (Table 1a).

##### 

**Feasibility** All women will complete the 10-item CASI Assessment Evaluation (CAE), an established instrument designed to evaluate the feasibility of computer-based screening [40]. Originally designed to assess computer-based screening of intimate-partner violence, the CAE’s questions are relevant to assess feasibility of e-screening for prenatal mental health, and its content is more extensive than measures used in other studies evaluating different screening modalities in pregnant/postpartum women [38]. The CAE has demonstrated face, construct, and discriminant validity, and provides a standardized assessment of feasibility of e-technology [40]. Women in the intervention group will answer questions rating their experience of e-screening. Women in the control group will answer questions adapted from the CAE to assess their views of e-screening (for example, ‘Would you have been comfortable using a computer tablet to answer these questions?’).

##### 

**Acceptability** Questions adapted from other surveys of mental health screening acceptability [24,25,54] will be administered to women in both control and intervention groups to evaluate acceptability of the form of screening they completed. In addition, we will use semi-structured face-to-face or telephone-based interviews to determine views of feasibility and acceptability among a subset of 20 participants and 8 healthcare providers.

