## Purpose

### Objectives, research questions, and hypotheses

#### *Primary objective*

The primary objective of the study is to determine pregnant women’s and healthcare providers’ views of the feasibility and acceptability of mental health e-screening compared to paper-based screening.

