### Research questions and hypotheses

The specific research questions and hypotheses corresponding to the primary and secondary objectives are described in Table 1. Overall, we hypothesize that mental health e-screening in primary care maternity settings and high-risk antenatal units will be as or more feasible, acceptable, and capable of detecting depression, anxiety, and psychosocial risk compared to paper-based screening.

**Table 1 T1:** Primary and secondary objectives, research questions, and hypotheses

**a**				
**Primary objective**	**Research question**	**Outcome**	**Measures**	**Testable hypothesis**
To compare the feasibility and acceptability of mental health e-screening *versus* paper-based screening.	Is mental health e-screening as or more feasible and acceptable to pregnant women and their healthcare providers than paper-based screening?	Feasibility: % women in intervention and control groups reporting that screening is easily done as a component of routine prenatal care; mean CAE score	Quantitative:	Mean CAE scores and % of women responding affirmatively to questions of feasibility and acceptability will be similar or significantly higher in the intervention group (indicating greater feasibility/acceptability) compared to the control group
			Feasibility	
			Example (CAE): I liked/would like using the tablet to answer these questions	
		Acceptability: % of participants in intervention and control groups reporting that screening is acceptable; % of participants reporting that questions about emotional health were easy to understand and easy to navigate around on the tablet	Acceptability	
			Example: (1) I did not/would not like answering questions on a tablet because it felt/would feel impersonal	
			Qualitative:	
			Semi-structured interviews	
**b**				
**Secondary objective**	**Research question**	**Outcome**	**Measure**	**Testable hypotheses**

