### Analysis

#### *Primary outcome and description of sample*

Intention-to-treat analysis will be conducted for all analyses. We will use descriptive data (frequencies/95% CI; means/standard deviation) to describe the sample. Baseline differences in groups will be compared using independent t-tests (means) and chi-square tests (%) to determine the extent to which randomization was successful. Statistical significance for all analyses is set at *P* <0.05. We will use two-tailed independent t-tests to compare intervention and control group differences in mean scores of the CAE and chi-square tests to compare proportions of women in each group responding affirmatively to questions on feasibility and acceptability.

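### The between-arm test of mean CAE scores compares used with imagined tablet screening, not tablet with paper, and the acceptability items are described inconsistently.

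*Protocol article*

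**What the plan says.** All references are to the protocol article.

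- **Primary objective:** to determine women's and providers' "views of the feasibility and acceptability of mental health e-screening compared to paper-based screening".
- **Feasibility (Outcomes and measurement), intervention arm:** "Women in the intervention group will answer questions rating their experience of e-screening".
- **Feasibility, control arm:** "Women in the control group will answer questions adapted from the CAE to assess their views of e-screening". The example given there asks whether the woman would have been comfortable with a tablet.
- **Table 1a, CAE example item:** "I liked/would like using the tablet to answer these questions".
- **Acceptability (Outcomes and measurement):** adapted questions go to both arms "to evaluate acceptability of the form of screening they completed".
- **Table 1a, acceptability example item:** "I did not/would not like answering questions on a tablet because it felt/would feel impersonal". One acceptability outcome is the percentage "of participants reporting that questions about emotional health were easy to understand and easy to navigate around on the tablet".
- **Analysis, Primary outcome:** "We will use two-tailed independent t-tests to compare intervention and control group differences in mean scores of the CAE", with chi-square tests for the proportions answering affirmatively on feasibility and acceptability.
- **Table 1a, hypothesis:** CAE means and affirmative percentages will be similar or significantly higher in the intervention arm, which is taken to indicate greater feasibility and acceptability. The research question in the same row is whether e-screening does as well as, or better than, paper.

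**The concern.** A between-arm test answers a question about two modes only if each arm's score describes its own mode. On the CAE, both arms score the same mode. Intervention women have completed the ALPHA and EPDS on the tablet, and control women are asked how they would have found doing so. The paper assessment that control women completed receives no CAE score.

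What is at stake is the interpretation fixed in Table 1a. A CAE result favouring the intervention arm, or showing no difference, would be reported as evidence that e-screening is at least as feasible as paper, although the scores contain no information on paper. Analysis cannot repair this. Women complete the assessment and its questionnaires on a single occasion, so ratings of paper that are not collected then are lost.

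The acceptability items raise a different problem. The Methods text and Table 1a disagree about which mode the control arm is rating. If the Table 1a wording is the one built into the survey, those items share the CAE's fault.

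**Working it through.** **1. The plan's own figure.** The Sample size section uses the precision of a single proportion:

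- n = p(1 − p)(1.96/0.05)² = 0.85 × 0.15 × 39.2² = 195.92, rounded to 196.
- Allowing for 25% attrition: 196/(1 − 0.25) = 261.33, stated as 261 per group.
- Total: 2 × 261 = 522.

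The figures reproduce. They rest on a proportion in the intervention arm alone, so the wording of the control items does not enter them.

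**2. What the CAE contrast estimates.** Write T1 for the mean rating of the tablet assessment among women who completed it, T0 for the mean rating that control women give to a tablet assessment they did not complete, and P for the mean rating that control women would give to the paper assessment they did complete.

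- Objective: T1 − P.
- Planned t-test: T1 − T0.
- Discrepancy: (T1 − P) − (T1 − T0) = T0 − P.

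Randomization makes T1 − T0 a fair estimate of something, namely how completing the assessment on a tablet changes a woman's view of tablet screening. It does not make it an estimate of T1 − P. The CAE never collects P, so T0 − P can be neither estimated nor bounded from CAE data. If control women thought paper excellent and expected to like a tablet, or thought paper poor and expected to like a tablet equally, T1 − T0 would be identical.

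**3. What the test could detect.** For a two-sided 5% test with 80% power, the detectable standardized difference is (1.960 + 0.842) × √(2/n per arm):

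- n = 261: 2.802 × √(2/261) = 0.245 SD.
- n = 196: 2.802 × √(2/196) = 0.283 SD.

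The trial can therefore declare significance for a modest gap between T1 and T0. The documents do not indicate how large that gap would be, so these figures describe the sensitivity of the test and not an amount of bias.

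**4. Acceptability, set side by side.**

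| Source | What control women rate |
|---|---|
| Methods text, Acceptability | The form they completed, hence paper |
| Table 1a, example item | Tablet, in the conditional |
| Table 1a, navigation outcome | Tablet; no paper counterpart given |
| Table 1a, percentage finding screening acceptable | Mode not specified; both arms |

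The first row cannot be reconciled with the second and third as they stand.

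**5. Carry-over.** The Secondary outcomes section seeks factors associated with feasibility for each form of screening, and the analysis dichotomizes feasibility from the CAE. A control woman's CAE score cannot stand for the feasibility of paper there either.

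**The case against.** A reader might infer that the primary comparison never sets e-screening against paper and that the primary objective cannot be answered. The documents do not support that, for four reasons.

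- Table 1a also lists, for both arms, the percentage who say screening fits easily into routine prenatal care and the percentage who find it acceptable. Neither names a mode, and the Analysis section compares such proportions by chi-square.
- The Methods text says acceptability items rate the completed form. One example item does not establish how the rest of a questionnaire that is not shown is worded.
- The interviews ask each arm about its own mode, and the objective also covers providers' views, which the CAE does not collect.
- The 85% feasibility criteria in the Sample size section apply to the intervention arm alone.

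All of this stands, and it limits the point to the CAE test and the tablet-worded items. It does not rescue the CAE test: the interviews cover about 10 control women, and no mode-neutral percentage is given precedence over the CAE.

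It can also be said that control women know the tablet, since they consent on it and return to it after the paper forms. Their views are therefore informed, and the contrast is not purely experience against expectation. They still did not complete the ALPHA and EPDS on it, and they are still not rating paper.

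A reader might add a multiplicity argument. The plan tests the CAE as one mean and gives no count of separately tested items, so no error rate can be attached to it.

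**Conclusion.** The point holds in a limited form. The comparison of mean CAE scores contains no rating of paper, and Table 1a's reading of it as relative feasibility against paper is invalid whichever way the result falls. This follows from the Feasibility text and the Table 1a example item and needs no numerical assumption. The acceptability defect is an inconsistency between the Methods text and Table 1a. Whether it affects the data depends on the final item wording, which is not shown.

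The size of any misleading effect is unknown. What can be said is that a gap of about 0.25 SD (261 per arm) to 0.28 SD (196 per arm) between used and imagined tablet ratings would be declared significant with 80% power. The correction matters because the CAE is the only named scale and the only mean-score test in the primary outcome, and because the missing ratings cannot be recovered later.

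**What to change.** 1. Give each arm parallel CAE-type items about the mode it completed, such as liking the tablet (intervention) or the paper form (control) for answering the questions. Base the between-arm feasibility test on those items only.
2. Keep the control arm's conditional tablet items, but report them as a description of control women's views and do not test them against the intervention arm.
3. Align Table 1a with the Methods text. Word the acceptability example for the form completed. Either give the navigation outcome a paper counterpart or restrict it to the intervention arm.
4. Reword the Table 1a hypothesis so that its CAE part refers to the parallel items, and use the same items where feasibility is modelled for each form of screening.

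The cost is rewording some survey screens and amending Table 1a, the Feasibility paragraph and the analysis text. The sample size is unaffected. The downside is that the control-arm items move further from the published CAE, so the validity cited for it carries over less directly. The control version is already an adaptation, so this is a matter of degree.

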### Secondary outcomes

The five secondary outcomes are (see measures in Table 1b):

(1) the proportion of pregnant women scoring 13 or more on the total EPDS, 4 or more on the anxiety subscale, and identified as some or high psychosocial risk on the ALPHA;

(2) the level of disclosure as assessed by mean scores on the Perceived Risk and Perceived Utility subscales of the Disclosure Expectations Scale (DES) [55]. The DES is an 8-item scale designed for evaluation of the perceived risk (items 1, 2, 4, and 5) and benefit (items 3, 6, 7, and 8) of disclosure. Convergent validity of the subscales has been demonstrated with other measures of self-disclosure, as well as psychological distress, and intention to seek mental healthcare [55];

(3) description of factors that significantly increase the odds of acceptability, feasibility, and disclosure related to each form of screening;

(4) psychometric properties (for example, Cronbach’s alpha, sensitivity, specificity, positive and negative predictive values) of the e-version of the EPDS and ALPHA. A scoring algorithm does not currently exist for the ALPHA (for example, the trained provider subjectively judges risk based on responses); however, an algorithm would promote standardization in clinical decision-making and efficiency since a score could be calculated as part of e-screening. We plan further tool development comprising derivation of a quantitative scoring method for classifying women into psychosocial risk categories; and

(5) cost-effectiveness of detecting clinical depression and anxiety in e-screening *versus* usual screening (that is, equipment and human resource costs of e-screening *versus* paper-based - see Secondary outcomes).

#### Sample size

##### 

**Determination of sample size** Because no data are available to guide estimation of a minimal clinically important difference in ‘true’ cases detected through e-screening a ‘confidence interval (CI) approach’ [56] was used. Based on high levels of acceptability and disclosure reported using computer screening [39,40], e-screening would be feasible if, in the intervention group: (1) 85% of women indicated that they were able to tell the truth on all items (Q7 CAE); (2) 85% scored 4 to 8 on the Risk subscale of the DES (no/slight perceived risk to disclosure); and (3) 85% scored 16 to 20 on the DES Utility subscale (for example, disclosure moderately or very beneficial). The sample size calculation (Table 2) indicates that 261 women per group (*n* = 522) is required.

**Table 2 T2:** Sample size determination

**Using the calculation of a confidence interval for a proportion, a 95% CI and a margin of error of 0.05:**	**Accounting for an estimated attrition/loss to follow-up of 25% based on other reported rates in pregnant and postpartum women (55,66):**
p = a priori estimate of % of interest; *n* = sample size	*n* = total sample size; L = attrition rate + loss-to-follow up
*n* = p(1-p) [1.96/.05]^2^	N_new_ = n/(1-L)
*n* = 0.85(1–0.85) [39.2]^2^	N_new_ = 196/(1–0.25)
*n* = 196	N_new_ =261

Therefore a minimum of 261 women per group would be required.

##### 

**Feasibility of achieving sample size** The maternity clinics conduct initial prenatal visits for a total of 50 women per month across all clinics. The number of new patients on the high-risk antenatal unit is similar at 45 women per month. Clinic staff estimates that roughly 4% of women would be ineligible due to language (96% eligible = 91 women per month). A conservative estimation of 50% participation rate [57,58] would yield 46 women per month. Thus, recruitment of women is expected to take 12 months.

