**Methods/Design:**

The primary objective of this randomized, parallel-group, superiority trial is to evaluate the feasibility and acceptability of a computer tablet-based prenatal psychosocial assessment (e-screening) compared to paper-based screening. Secondary objectives are to compare the two modes of screening on: (1) the level of detection of prenatal depression and anxiety symptoms and psychosocial risk; (2) the level of disclosure of symptoms; (3) the factors associated with feasibility, acceptability, and disclosure; (4) the psychometric properties of the e-version of the assessment tools; and (5) cost-effectiveness. A sample of 542 women will be recruited from large, primary care maternity clinics and a high-risk antenatal unit in an urban Canadian city. Pregnant women are eligible to participate if they: (1) receive care at one of the recruitment sites; (2) are able to speak/read English; (3) are willing to be randomized to e-screening; and (4) are willing to participate in a follow-up diagnostic interview within 1 week of recruitment. Allocation is by computer-generated randomization. Women in the intervention group will complete an online psychosocial assessment on a computer tablet, while those in the control group will complete the same assessment in paper-based form. All women will complete baseline questionnaires at the time of recruitment and will participate in a diagnostic interview within 1 week of recruitment. Research assistants conducting diagnostic interviews and physicians will be blinded. A qualitative descriptive study involving healthcare providers from the recruitment sites and women will provide data on feasibility and acceptability of the intervention. We hypothesize that mental health e-screening in primary care maternity settings and high-risk antenatal units will be as or more feasible, acceptable, and capable of detecting depression, anxiety, and psychosocial risk compared to paper-based screening.

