#### *Data collection procedures*

Procedures related to completion of the psychosocial assessment and baseline questionnaire are described in Procedures. Women will complete the psychosocial assessment on a single occasion. The content and order of individual questions in the e-version of the instruments will be identical to the paper-based version. Women select responses by touching the screen. If a woman does not answer a question, she will be prompted to respond before she can proceed. This is to mimic the usual screening process where the nurse would ask the woman to respond to a missing answer. A ‘SUBMIT’ button at the bottom of the baseline questionnaire will allow women to submit their responses.

The order of material on the tablet will be: (1) Participant Information Letter and Consent; (2) preamble describing the importance of screening and the follow-up with the healthcare provider; (3) ALPHA and EPDS; (4) the CAE, DES, and questions related to acceptability, feasibility, and disclosure; and (5) baseline questionnaire. The content of the baseline questionnaire includes questions that represent factors associated with prenatal mental health or disclosure of mental health concerns, and includes: (1) demographics (age, parity, marital status, education, income, ethnicity, country of birth, and length of time in Canada); (2) obstetrical history (current and past, including use of fertility treatments); (3) mental health history (diagnoses, treatment); (4) level of comfort with technology (for example, laptop, tablet); (5) quality of relationship with perinatal care provider; (6) level of social support, experience of talking with doctor/nurse/midwife about emotional health; and (7) adverse childhood experiences (using ACES questionnaire [48]). With the exception of the ACES (http://acestudy.org/ace_score), questions were derived from the All Our Babies longitudinal birth cohort study (http://www.prehot.org/The%20All%20Our%20Babies%20Study/) and the Maternity Experiences Survey (http://www.phac-aspc.gc.ca/rhs-ssg/survey-eng.php). Participants are required to answer all fields except for income, thus limiting the issue of missing data. Data for the economic evaluation will be collected from program accounts for technology and software costs, and by interviewing clinic staff to estimate clinic operation costs for the two alternatives. We will use a healthcare perspective and all costs will be shown in 2014 values.

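### The recruitment total is given as both 542 and 522, and the size rests on one-arm precision, an unsupported 25% loss and an 85% criterion that the planned analysis does not use

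*Protocol article*

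**What the plan says.** **Totals.** The abstract (Methods/Design) states: "A sample of 542 women will be recruited from large, primary care maternity clinics and a high-risk antenatal unit". The Sample size section states: "The sample size calculation (Table 2) indicates that 261 women per group", with 522 in brackets as the total, and Table 2 ends: "Therefore a minimum of 261 women per group would be required".

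**Basis.** Table 2 is headed: "Using the calculation of a confidence interval for a proportion, a 95% CI and a margin of error of 0.05". It uses p = 0.85, defined as "p = a priori estimate of % of interest", and then inflates for 25% attrition or loss to follow-up.

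**Criteria.** The text before Table 2 would call e-screening feasible if three conditions hold in the intervention group. The first is that "85% of women indicated that they were able to tell the truth on all items" (CAE question 7). The other two are that 85% score in a favourable range on the DES Risk subscale and 85% on the DES Utility subscale.

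**Design and analysis.** Study design describes a parallel-group superiority trial. The primary analysis compares arms, with t-tests for mean CAE scores and chi-square tests for proportions, at P < 0.05. The DES appears under Secondary outcomes, as mean subscale scores compared by t-test.

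**Timing.** Data collection procedures states: "Women will complete the psychosocial assessment on a single occasion". The CAE and DES follow the ALPHA and EPDS in the same tablet sequence, and every field except income must be answered. The only later quantitative contact is the MINI: by telephone within a week for clinic women, and at recruitment for antenatal-unit women.

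**The concern.** Four things in the sample size section do not fit the rest of the protocol.

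1. Two totals are given, so a reader cannot tell when recruitment is complete. The 20 women to be interviewed are the obvious explanation for the gap of 20, but Outcomes and measurement calls them a subset of participants and the qualitative section draws 10 from each trial group. They are already counted.
2. The stated ±5 points is the precision of one arm's proportion, whereas the primary question is a difference between arms, which is estimated less precisely.
3. An allowance for loss to follow-up is applied to outcomes that have no follow-up.
4. The criteria that justify the size do not reappear in the Analysis section, and two of the three come from a scale analysed elsewhere as a secondary outcome.

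At stake is whether readers know the target, know how precise the primary comparison will be, and can tell how feasibility will be judged.

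**Working it through.** **Reproducing Table 2.** Inputs from Table 2: p = 0.85, margin 0.05, z = 1.96, loss 0.25.
- n = 0.85 × 0.15 × (1.96/0.05)² = 0.1275 × 39.2² = 195.9, given as 196.
- 196 / (1 − 0.25) = 261.3, given as 261.
- 2 × 261 = 522. The figure reproduces.

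**The 542.** 542 − 522 = 20, or 3.8% of 522. At 1:1 allocation, 542 is 271 per arm. To reach 271 from 196, the loss would have to be 1 − 196/271 = 27.7%, which the protocol does not state. Projected accrual of 46 a month for 12 months is 552, which covers both totals and so does not settle which is meant.

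**Precision of one arm and of the difference.** Assumption: 85% in each arm. One arm: 1.96 × √(0.1275/n). Difference: 1.96 × √(2 × 0.1275/n).

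| Women per arm | One arm | Difference |
|---|---|---|
| 196 | ±5.0 points | ±7.1 points |
| 261 | ±4.3 points | ±6.1 points |

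**Power and detectable difference.** The protocol gives no between-arm effect, so these rates are illustrative (two-sided 0.05, normal approximation, pooled variance under the null).
- 85% against 90% at 261 per arm: the pooled standard error is √(2 × 0.875 × 0.125/261) = 0.02895, and the standard error under the alternative is √((0.1275 + 0.09)/261) = 0.02887. Power = Φ((0.05 − 1.96 × 0.02895)/0.02887) = Φ(−0.23) = 0.41. At 196 per arm it is 0.32. About 686 per arm would be needed for 80% power.
- With 80% power, 261 per arm detects 85% against about 75% downward, or about 93% upward.

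**The 25%.** CAE question 7 and both DES subscales are answered in the sitting in which the woman is randomized. If no one is lost before submission, the intervention-arm margin is the ±4.3 points in the table; if 25% are lost, it is ±5.0.

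**The 85% criteria.** Read literally, a criterion passes if at least 85% of women meet it. At n = 261, 0.85 × 261 = 221.85, so 222 women are needed. Exact binomial pass probabilities for one criterion:

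| True rate | n = 196 (needs 167) | n = 261 (needs 222) |
|---|---|---|
| 80% | 0.04 | 0.02 |
| 85% | 0.52 | 0.53 |
| 87% | 0.81 | 0.85 |
| 90% | 0.99 | 0.996 |

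A value near one half in the 85% row is what follows when the threshold equals the planning value. Other readings give other answers. At n = 196 and a true 85%, the pass probability is 0.98 if the 95% interval need only reach 85%, and 0.03 if its lower limit must be at least 85%. The protocol does not say which applies.

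**The case against.** **On the totals.** The protocol calls 261 per group a minimum, and 542 meets it. The gap is small and may be a deliberate margin. That stands as a possible explanation, but the text does not give it.

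**On the sizing basis.** The protocol says openly that it used a confidence-interval approach, because no data were available to set a minimal important difference in true cases detected. That is a fair reason for not doing a power calculation on detection. But detection is a secondary outcome, and the reason does not cover the primary between-arm comparison of feasibility and acceptability.

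**On attrition.** A reader might infer that loss cannot occur at all for same-sitting outcomes. The documents do not support that. Clinic women use the tablet while waiting to be called, the SUBMIT button comes at the end of the baseline questionnaire, and nothing is stored on the tablet. A woman who stops midway could lose her CAE and DES data. Some loss is therefore possible; what lacks support is 25%, taken from rates of attrition and loss to follow-up. The protocol does not say that the allowance was meant for the MINI, and that reading would fit poorly, because antenatal-unit women (45 of the 95 monthly intake) have the MINI at recruitment.

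**On the 85% criteria.** A reader might infer that the feasibility decision is a coin-flip. That holds only for a literal rule of observed 85% or more and a true rate of exactly 85%. Multiplying the three probabilities would also assume independence between two subscales of one questionnaire and an item from the same sitting. The detail of how the criteria are judged may sit in a document not shown. What stands is that 85% does two jobs, and that the analysis the article describes does something else with these measures.

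**Conclusion.** The point holds and should be fixed, though no planned analysis is invalidated by it.

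- The protocol gives two totals, 542 and 522, and does not reconcile them. This needs no assumption.
- Table 2's arithmetic is correct. Calling this a calculation error would be wrong; the fault lies in what was sized and in the inputs.
- The stated ±5 points is not the precision of the primary comparison, which is ±7.1 points at 196 per arm or ±6.1 at 261. This assumes 85% in each arm. The power of 0.41 rests on the illustrative pair 85% and 90%. It does not show that the trial is too small, because the protocol names no target difference.
- The 25% is unsupported for CAE question 7 and the DES. The ±4.3 points at 261 assumes no loss.
- The 85% criteria are not evaluated in the Analysis section, where the DES is compared as mean scores under a secondary outcome. The pass probability of 0.53 is conditional on the literal reading and a true rate of 85%.

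**What to change.** 1. State one total in the abstract and the Sample size section: 522, or 542 with its reason.
2. Say that the size was set for the precision of one proportion in the intervention arm. Add the between-arm margin for 261 per arm (±6.1 points at an assumed 85%) and the detectable difference (about 85% against 75%, or 93% upward, at 80% power), with the rates labelled as assumptions.
3. Justify the 25% for outcomes collected in the same sitting, or replace it with an allowance for unsubmitted sessions and restate the margin.
4. Either report the three criteria in the Analysis as intervention-arm estimates with 95% confidence intervals, or say that 85% is a planning value only. If a pass rule is kept, set its threshold apart from the planning value and state its pass probabilities. Requiring the lower 95% limit to reach 80% would not achieve this: at n = 261 with Wilson or exact limits it again needs 222 women, so it passes with the same probability of 0.53 at a true 85% (0.60 with Wald limits).

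The cost is wording, with no more women needed than planned. The downside is that the stated precision for the primary comparison looks less favourable than ±5 points.
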